#### Retention

Strategies to support retention are focused around consultation during the trial design process, adapting the therapy/process to fit the participants’ requirements, developing staff skillset, and attending to the participant experience throughout the trial. With the explicit purpose of maximising retention, the design of the trial and the associated materials were discussed with the aforementioned HD steering group and designed by HD clinicians; this helped the intervention meets the specific needs of people affected by HD. Examples of this included the provision of multiple formats of participant materials (paper, pdf), a facilitated intervention, removal of travel requirements (i.e., home visits or remote contact), posted materials, additional carer support sessions, and direct contact with the research team through multiple methods of communication. To support retention further, all staff involved in the trial who interact with participants will receive specialist training to supplement any existing clinical experience in supporting people and families affected by HD. A further key part of the retention aspect of the study is attending to participant experiences and needs. Further to the general adaptations of the study and training of staff, each participant has an individual psychological formulation, generated by a clinical psychologist from a clinical interview and cognitive screening. This provides an opportunity to tailor further the trial to suit them, for example through identifying any existing strategies that participants use to support their memory and planning. For participants in the intervention arm, this is further built upon through the use of the COM-B model and by collaboratively problem-solving potential barriers to participating in the intervention.

### Feasibility outcomes

#### Primary outcome measures

Feasibility will be assessed using the following:1. Recruitment rate (% eligible participants who consent) by the end of the study.2. Retention of participants in both arms of the trial (% who remain in the study at 3- and 6-month follow-up).

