### Participants, eligibility, recruitment and consent

Participants will primarily be recruited across several counties in the UK (Leicestershire, Nottinghamshire, Northamptonshire, Lincolnshire, and Derbyshire) via either local NHS Trusts or UK HD charities (e.g., the Huntington’s Disease Association).

As this is a feasibility study, a formal power calculation is not appropriate given that the parameters for estimation are unclear due to the lack of previous research in this area, and the aim is primarily to assess feasibility outcomes. Consequently, we have assumed that 12 participants per group will be sufficient to determine reliably the primary feasibility outcomes [28]. The total recruitment target is set at 30 HD participants (15 per arm) to allow for expected attrition rates. With the inclusion of carers, the sample size is aimed at 36.

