#### Secondary outcome measures

Further feasibility outcomes are as follows:1. Acceptability of the intervention assessed with Likert ratings 0–5 on dimensions of readability, clarity, effort, enjoyment, concentration, helpfulness, and progress regarding therapy materials at 2-week post-intervention and qualitative interviews within 1-month post-intervention.2. Acceptability and suitability of outcome measures assessed with a Likert scale at 6 months, qualitative interviews, and % willing to complete the measures at each timepoint (i.e., baseline, within two weeks after the intervention, 3- and 6-month follow-ups). The acceptability rating scale for the outcome measures will cover overall acceptability, acceptability of the nature of the questions asked in the measures, the time it took to complete the measures, and the number of times they were asked to complete the measures.3. Adherence to the intervention (% of activities accomplished) by the end of the study. This will be determined from the number of items completed on the adherence checklists completed by the facilitators after each session.

In terms of criteria required for progression to a trial, we will establish the feasibility of our study design and intervention using a red-amber-green light system (or otherwise named stop-amend-go). We will use the percentages gained from recruitment, retention, adherence, and acceptability measures and establish feasibility using the following progression criteria:

Definite go (‘green light’) defined as follows: ≥ 60% of eligible participants consent to feasibility trial. ≥ 70% retention of consented participants in both arms of the trial at 3- and 6-month follow-up. ≥ 90% of at least one primary outcome measure is completed, including 6-month follow-up. > 75% of all activities in intervention will be undertaken. > 75% of participants who complete the intervention will agree that the overall intervention is acceptable.

*Amber — for further discussion and modification* as follows:40–59% of eligible participants consent to feasibility trial.50–69% retention of consented participants in both arms of the trial at 3- and 6-month follow-up.70–89% of at least one primary outcome measure completed.60–75% of all activities in intervention will be undertaken.60–75% of participants who complete the intervention will agree that the overall intervention is acceptable.

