Definite stop (‘red light’) defined as follows: < 40% of eligible participants consent to feasibility trial. < 50% retention of consented participants in both arms of the trial at 3- and 6-month follow-up. < 70% of both primary outcome measures are not completed. < 60% of all activities in intervention will be accomplished. < 60% of participants who complete the intervention consider the overall intervention to be acceptable.

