## Discussion

The protocol has been developed as a result of the lack of evidenced interventions for this client group, the prominence of anxiety in clinical presentations, and the negative effects of anxiety on a range of health outcomes for pwHD. In putting together the proposal, we have attended to the needs and views of people affected by HD on the way information is presented.

A number of aspects of the protocol may need to be revised after this initial study, - for example the pace of the intervention, the format of the manual, or the nature of the interaction with the healthcare professional. However, the key indicators of whether this intervention should and could progress to a full trial -  such as our ability to recruit, to support the intervention in a remote fashion rather than in a more traditional (e.g., individual face to face) format, and to see the intervention completed - are the more substantive issues.

Guided self-help is considered a cost-effective psychological therapy for anxiety as it only involves support from a psychological therapist to ‘guide’ the patient to use a self-help intervention. While we have not included any economic evaluation as part of this protocol, we accept that indicators which could be used to assess the cost-effectiveness of the intervention (e.g., less time out of work and less frequent contact with health care services) would need to be addressed in a further trial. Moreover, while we would argue that the provision of psychological interventions for people with HD is important from a health inequality perspective (see [41, 42]), we also accept the limitations of individually focused interventions. Improving psychological well-being, including reducing anxiety, for this group also involves a more radical approach to conceptualising psychological distress from all perspectives — individual and societal [43].

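### The progression rule scores recruitment only as a consent percentage, so the target of 30 plays no part in the go, amend or stop decision

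*Protocol article*

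**What the plan says.** The Aims section makes the feasibility of recruitment and retention the primary objective, and lists as a further objective whether the criteria for a definitive trial are met.

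Under Primary outcome measures, the recruitment outcome is "Recruitment rate (% eligible participants who consent) by the end of the study".

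Under Secondary outcome measures, the basis of the decision is stated: "We will use the percentages gained from recruitment, retention, adherence, and acceptability measures and establish feasibility using the following progression criteria". The recruitment bands are:

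- green: "≥ 60% of eligible participants consent to feasibility trial"
- amber: "40–59% of eligible participants consent to feasibility trial"
- red: "< 40% of eligible participants consent to feasibility trial"

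The other four criteria (retention, completion of a primary outcome measure, activities undertaken, acceptability) are percentages too. Retention, for example, is green at "≥ 70% retention of consented participants in both arms of the trial at 3- and 6-month follow-up".

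The sample size stands elsewhere, under Participants, eligibility, recruitment and consent. There, 12 per group is assumed to be enough for the primary feasibility outcomes, and "The total recruitment target is set at 30 HD participants (15 per arm) to allow for expected attrition rates". Neither 30 nor 12 per group appears in any feasibility outcome or progression criterion.

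The Discussion lists the key indicators of whether the work should and could go on to a full trial, "such as our ability to recruit, to support the intervention in a remote fashion".

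**The concern.** A consent percentage measures willingness among the eligible people who were found. It does not say how many were found or how many were randomised. A full trial needs both: people who agree, and enough of them. The rule as printed registers only the first.

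The decision at stake is whether to proceed to a definitive trial. A green recruitment score could come from a handful of willing people. A trial that filled all its places could be scored amber or red because it approached many people. The recruitment colour is thus detached from the one recruitment figure that the plan sets for itself.

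**Working it through.** **Inputs.** Target 30, or 15 per arm, and 12 per group judged sufficient (Participants, eligibility, recruitment and consent). Allocation 1:1 (Design and setting). Recruitment bands at least 60%, 40–59% and under 40% of eligible people; green retention at least 70% (Secondary outcome measures). The expected attrition rate is not stated, so it is inferred below.

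**1. The plan's own figure.** Number per arm = 12 / (1 − d), rounded up. With d = 0.20, 12 / 0.80 = 15 per arm, or 30 in total, which reproduces the target. Read exactly, 15 implies d = 1 − 12/15 = 20%. A loss of 15% also rounds up to 15; 25% gives 16 and 30% gives 18.

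**2. Green has no floor on numbers.** Score = consenting / eligible. Assume that everyone who consents is randomised:

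| Consenting / eligible | Percentage | Colour | Share of 30 |
|---|---|---|---|
| 3 / 5 | 60% | green | 10% |
| 6 / 10 | 60% | green | 20% |
| 12 / 20 | 60% | green | 40% |
| 30 / 50 | 60% | green | 100% |
| 30 / 60 | 50% | amber | 100% |
| 30 / 80 | 37.5% | red | 100% |

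The first four rows score alike, although they run from a tenth of the target to all of it. The last three all reach 30, yet take three different colours.

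**3. Whether the whole rule can be green at low numbers.** Suppose that 12 eligible people are found, 9 consent and 8 are randomised, 4 per arm.

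- Recruitment: 9/12 = 75%, green.
- Retention with all 8 kept: 8/8 = 100%, or 8/9 = 89% if the consenter who was not randomised stays in the denominator. Both are green.
- Measure completion, activities and acceptability are percentages among those present and can all be green.
- Share of target: 8/30 = 27%. Per group: 4 of 12, one third.

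**4. Precision at small numbers.** Exact (Clopper–Pearson) 95% intervals for an observed 60% are 26–88% at 6/10, 36–81% at 12/20 and 45–74% at 30/50. Take a true consent rate of 40%, the bottom of amber, and independent decisions. The binomial chance of scoring green is then 16.6% with 10 eligible people, 5.7% with 20 and 0.3% with 50. Finding few eligible people therefore makes a mistaken green more likely.

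**5. Whether 24 randomised would protect 12 per group.** With 20% loss, 24 × 0.80 = 19.2, under 10 per arm. At the lowest green retention, 24 × 0.70 = 16.8, about 8 per arm. Any loss at all takes 24 below 12 per group.

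**The case against.** The strongest reply is that the numbers will be in plain view. The Data analysis section commits to descriptive statistics on recruitment and retention, the Aims include describing screening results, and a CONSORT flow diagram is used. The progression assessment is also to be informed by qualitative feedback. A trial with 8 randomised would be visibly so. A reader might infer from the printed rule that a shortfall would be concealed, or that the team would in fact proceed at 8 of 30. The documents support neither. What remains is that the article prints the whole decision rule with its cut-offs and says that percentages establish feasibility. Reporting a count beside the rule does not bring it into the rule.

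A reader might also infer that too few eligible people is the likelier failure, more so than refusal, because eligibility is narrow and recruitment is primarily from a few counties. The documents give no pool size, referral volume or refusal rate. Charity routes also use websites and social media, and the abstract speaks of recruitment across the UK. Scarcity is a possibility that the rule cannot register, not a forecast.

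Nor is the absence of a recruitment period or accrual rate a fault here. A condensed article may leave these to the full protocol, and the figures are not shown.

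Finally, the 9-of-12 case is constructed, and its order is tidier than the Procedure section, where consent is taken before the diagnostic interview confirms eligibility. The conclusion does not depend on that order. Counting only the 8 randomised against the same 12 gives 67%, still green.

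**Conclusion.** The point holds as a flaw in a fully stated decision rule. The consent percentage is the only recruitment criterion, all five criteria are percentages, and the target of 30 has no role in the verdict. On the printed cut-offs, an overall green is attainable at 27% of target, while full recruitment can score amber or red. This sits badly with a primary objective about recruitment and with the Discussion's own list of key indicators.

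The scores follow from the cut-offs by arithmetic. The example counts are illustrations with no probability attached, and an overall green also needs the other four criteria to be met. The 20% attrition is inferred from 12 and 15, not stated. The consent percentage itself is a sound measure of willingness, and nothing here argues for dropping it. Label: cheap improvement.

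**What to change.** Keep the consent percentage, described as a measure of willingness. Add a green, amber and red criterion on the number randomised against the target of 30 by the end of recruitment.

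The team should set the cut-offs and justify them, stating the attrition assumed, so that green is consistent with 12 per group remaining after that attrition. A green cut-off of 24 randomised would fail this test, because 12 per group is the number needed after losses. The existing 40% red boundary should not be carried over without its own argument: it is a share of eligible people who consent, which is a different quantity from a share of the target.

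Report the number randomised per month descriptively, as the accrual estimate for the full trial.

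The cost is one added line per colour band and a short table from the randomisation dates. The downside is that a go becomes harder to reach.

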On contact with the research team, the participant will be given a further verbal description of the study and have any questions answered. If the participant agrees to go ahead, a face-to-face appointment to take written consent will then be arranged. As part of the consent process, participants will be informed that they are free to discontinue their involvement in the study at any point. Currently, the authors are also pursuing the option of adding remote verbal consent to the study by utilising videoconferencing recording, which will be subject to agreement by the NHS ethics committee. Following consent, potential participants with HD will initially be checked for basic eligibility criteria. If a person meets those basic criteria, then consent will be taken to proceed to the next step of the project. This will involve a clinical diagnostic interview with a clinical psychologist which will be undertaken at a time convenient for the participants, to ascertain whether they meet the *Diagnostic and Statistical Manual of Mental Disorders* (DSM-V; [30]) criteria for an anxiety disorder; this is needed to establish whether full criteria for eligibility will be met. Clinically relevant information gained from this interview will also form part of the treatment formulation plan for those who are allocated to the intervention arm of the study. At this assessment point, if the threshold for an anxiety disorder is reached, then cognitive functioning will also be assessed using a brief measure (the Montreal Cognitive Assessment, MoCA; [31]). The purpose of this measure is both to characterise the sample and enable therapists to understand any difficulties so the intervention can be tailored appropriately. The clinical psychologist will also make a judgement, based on both the cognitive assessment and the interview, whether the potential participant fits the eligibility for cognitive and communication abilities necessary to proceed with the intervention.

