Data will be stored in Microsoft Access on a corporate server which is subject to regular back-up routines. In terms of ensuring data quality, as all outcome measures are completed in paper format initially and then inputted into Microsoft Access, the academic researchers, prior to analysis, will cross-check paper versions with electronic data entries for any potential input errors. Moreover, no total scores will be inputted for each measure; instead, Access formulas will be used to calculate these for each measure. This represents a prospective approach to managing missing data. As most of the feasibility data to be collected will be known to the research team (e.g., recruitment and retention), the potential for missing data is limited. However, the number of missing responses to the Likert scale assessments will be noted.

All qualitative data transcripts will be transcribed verbatim by the senior research associate, and each researcher will code them individually. Once initial codes are developed, themes will be established and checked with each researcher to ensure inter-rater reliability. Given this is a small-scale feasibility project, no data monitoring committee is being convened for this trial; however, a Lancaster University academic external to the research team will assess adherence to the agreed data analytic strategy and the robustness of the results.

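### The primary recruitment rate divides by eligible people, but full eligibility is known only after consent, so the go/stop criterion cannot return amber or red as worded

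*Protocol article*

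**What the plan says.** Under Primary outcome measures, the first feasibility outcome is "Recruitment rate (% eligible participants who consent) by the end of the study". The progression criteria under Secondary outcome measures use the same quantity. Green is "≥ 60% of eligible participants consent to feasibility trial", amber is "40–59% of eligible participants consent to feasibility trial" and red is "< 40% of eligible participants consent to feasibility trial".

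The Procedure section fixes the order of events. After a verbal description of the study, "If the participant agrees to go ahead, a face-to-face appointment to take written consent will then be arranged". Then: "Following consent, potential participants with HD will initially be checked for basic eligibility criteria". Those who pass are asked for a further consent to continue. Next comes the diagnostic interview with a clinical psychologist, of which the article says that "this is needed to establish whether full criteria for eligibility will be met". If the anxiety threshold is reached, the MoCA is given, and the psychologist judges whether cognition and communication are adequate.

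The Eligibility section makes a SCID-5 anxiety diagnosis an inclusion criterion and significant cognitive or communication impairment an exclusion criterion. Both are therefore settled after the second consent. Before any consent, the NHS route has people whom clinical staff think likely to qualify, and the charity route has people who answer an advertisement.

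**The concern.** A recruitment rate is meant to show how many of the people who could join choose to do so. That needs a denominator containing people who said no. Here, membership of the denominator depends on assessments given only to people who said yes.

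This is the first of two primary outcomes and the first line of the stop/go rule, and recruitment is part of the primary objective. A criterion that cannot return amber or red gives no information about whether a full trial could recruit. If the team instead settles on some other denominator once the data are in, the colour depends on a choice made after seeing the results.

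**Working it through.** The protocol states cut-offs but no expected recruitment rate, so there is no figure of its own to reproduce. The check orders the steps and computes the rate under each possible meaning of the definition. All counts below are assumed for illustration; only the cut-offs come from the document.

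**What is known at each step (Procedure and Eligibility sections)**

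| Step | Event | Eligibility known at that point |
|---|---|---|
| 1 | Identified by NHS staff, or responds to an advertisement | Apparent at most |
| 2 | First written consent | Apparent at most |
| 3 | Basic check | Basic criteria |
| 4 | Second consent | Basic criteria |
| 5 | Diagnostic interview | Anxiety diagnosis |
| 6 | MoCA and psychologist's judgement | All criteria |

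**Reading A: eligible means all criteria met.** Let E be the number confirmed at step 6. All E gave both consents, so the rate is E/E. With E = 30 it is 30/30 = 100%, green. Refusals at step 2 or step 4 do not change it, because those people never reach the interview.

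**Reading B: decliners who would have been eligible also count.** Let k be their number. The rate is E/(E + k), and k is not observed. Suppose 100 people appear eligible, 60 give first consent, all 60 go on to the interview and 30 are confirmed. The 40 decliners may contain anything from 0 to 40 eligible people:

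- k = 0: 30/30 = 100%, green.
- k = 40: 30/(30 + 40) = 42.9%, amber.
- The rate falls below 60% once k exceeds 30/0.60 − 30 = 20.
- It would fall below 40% only if k exceeded 30/0.40 − 30 = 45, which these counts do not allow.

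Green and amber both fit the same data, and nothing the trial collects can separate them.

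**Reading C: first consent among people who appear eligible.** In the same example this is 60/100 = 60%, green. In general it equals the first-stage uptake: 30% is red, 50% amber, 70% green.

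**Reading D: second consent among people passing the basic check.** This can fall below 100%, because someone may pass the check and then decline. But everyone in it has already consented once, so first-stage refusals are excluded. If second consent is assumed to run at 60% to 90%, the result is green throughout that range, whether first-stage uptake is 30%, 50% or 70%.

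**Comparison.** With first-stage uptake of 30% and second consent of 60% or more, the same trial is green under A (100%), red under C (30%) and green under D. The protocol does not say which is meant.

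**The case against.** The best counter-argument is that eligible is used loosely, for people whom clinical staff have pre-screened. That is natural on the NHS route and gives a computable rate (reading C). But the article does not say so, and Procedure separates people who look suitable from those who meet full criteria. It also cannot serve the charity route as it stands, since the pool reached by websites and social media is not countable.

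A second argument is that consent is staged, so a person can be found to meet the basic criteria and then refuse. This stands, and it limits the point: a reader might infer that the rate is 100% on every reading, and it is not. The 100% result belongs to eligibility in the full sense. Reading D escapes it, but the protocol does not name that rate and it leaves out first-stage refusals.

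Third, the article is condensed, its flow diagram is not in the text available here, and a screening log may exist in the full protocol. The absence of a log is not the complaint. No log or diagram can supply a SCID-5 result or a cognitive judgement for someone who declined.

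Three stronger inferences are not supported:

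- **The criterion would be red if randomised people were divided by those who appear eligible** (30/100 = 30% in the example). The stated numerator is consent, so this is not a reading of the stated criterion.
- **Uptake can be scaled by the 71% anxiety figure in the Background.** That is an upper prevalence among gene expansion carriers, not a SCID-5 pass rate among pre-screened consenters.
- **The Data analysis section is wrong on missing data.** Its words are "As most of the feasibility data to be collected will be known to the research team (e.g., recruitment and retention". It claims this for most of the data, not for every denominator, and needs no correction on this account.

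**Conclusion.** The point holds for the definition as worded. With eligible meaning that all criteria are met, the rate is 100% by construction and amber and red cannot occur. With decliners included, it cannot be computed; under the assumed counts it is bounded only between 43% and 100%. This rests on the order of steps in Procedure and needs no assumed figure. The illustrative counts show only how far the colour can move between readings.

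The consequence is confined to feasibility. Recruitment is one of five progression criteria, is analysed descriptively, and is weighed alongside qualitative feedback. No treatment comparison and no sample size is affected. Even so, a primary outcome and a stop rule that cannot signal a problem should be repaired before recruitment data are examined.

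**What to change.** Under Primary outcome measures and in the green, amber and red lists:

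1. **Denominator.** Define it as people recorded, before first written consent, as appearing to satisfy the criteria that can be checked without the SCID-5 and MoCA. On the NHS route these are the people clinical staff identify, kept as an anonymous count. On the charity route they are the people who contact the research team. Report the two routes separately, because the number reached by advertising is unknown.
2. **Numerator.** State that first written consent is the consent that counts.
3. **Bands.** Confirm, before data are seen, that the 60% and 40% cut-offs are intended for this rate. They were attached to a different denominator and should not carry over by default.
4. **Later stages.** Report separately, with reasons for loss, the percentages passing the basic check, giving the second consent, confirmed fully eligible and randomised.

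The cost is a revision of the wording, a small tally at recruiting clinics, and a recruitment rate that may look less favourable. Treatment, randomisation and target size are unchanged.
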